## Abstract

**Background:**

Polycystic Ovary Syndrome (PCOS) is a very common endocrine disorder with a variety of symptoms. Current treatment options include the contraceptive pill as well as metformin, however both treatments are limited to specific symptoms and have common side effects.

**Methods:**

This phase IV study is a monocentric, double blinded randomized clinical trial comparing the effects of six months of probiotic intervention to a placebo, with an additional open-label metformin arm as a positive control in a total of 180 participants with PCOS. The first of three visits is the screening visit, where inclusion/exclusion criteria are assessed. At the first visit, they are randomised into one of the three treatment arms equally and receive their study medication. After six months, all assessments from the first two visits are repeated. The primary endpoint is the change in free testosterone levels after the intervention, while secondary endpoints include changes in hormonal and metabolic parameters associated with PCOS as well as the gut microbial composition and diversity after intervention.

**Discussion:**

Based on new insights into the role of the gut microbiome in PCOS development, this study is exploring the potential of using probiotics to treat women with PCOS symptoms. If successful, this new therapy approach could open a new realm of possibilities for treating PCOS. To our knowledge, this is the first study comparing probiotic intervention with not only placebo treatment, but also metformin. This study has been approved by the ethics committee of the Medical University of Graz (EC number 32–230 ex 19/20).

**Registration:**

EudraCT number: 2020-000228-20. Clinicaltrials.gov identifier: NCT04593459.

**Protocol version:**

Version 1.5 dated 29th November 2021.

## Background

### PCOS and current therapeutic options

Polycystic Ovary Syndrome (PCOS) is a hormonal and metabolic disorder affecting up to 20% of women worldwide, depending on the diagnostic criteria used [1]. A very common definition of PCOS based on the revised Rotterdam criteria includes at least two out of three symptoms [2]: oligo-/amenorrhea, polycystic ovarian morphology and clinical or biochemical hyperandrogenism. Several comorbidities are also associated with PCOS, including depression, obesity, insulin resistance and Hashimoto’s thyroiditis [3, 4].

As the exact pathomechanisms of PCOS have not yet been established, therapeutic options mainly focus on specific symptoms. For obesity, insulin resistance and other metabolic symptoms, lifestyle changes, weight loss and off-label use of metformin are most commonly recommended and prescribed. Combined oral contraceptives (COCs) are most frequently used to alleviate hormonal symptoms (oligo-/amenorrhea, hirsutism) [3]. However, both metformin and COCs have potential side effects and contraindications, thereby limiting their use for the affected patients [3, 5].

### PCOS and microbiome interactions

Our group was among the first to discover lower bacterial abundances and significant differences in stool microbiome composition between women with PCOS and healthy controls in 2017 [6]. Since then, several studies have been published confirming these findings [7, 8]. The decreased alpha diversity of the gut microbiome has been found to correlate to total testosterone levels as well as the degree of hirsutism [7], while also being linked with insulin resistance, dyslipidemia as well as obesity [9, 10].

Gut microbiota also play a critical role in phytoestrogen metabolism in our body. For women with PCOS, the isoflavone metabolite equol may be of particular interest. Daidzein, one of the most abundant isoflavones found in plant products, can only be metabolized to equol via certain bacterial species in the human gut [11]. Equol in turn has been shown to bind to the estrogen receptors alpha and beta and to have anti-androgenic, anti-cancer and anti-inflammatory effects [12–15].

Several studies have already tested probiotic products for therapeutic use for women with PCOS [16–22]. Most studies had exactly 60 participants with PCOS randomized to two groups, however recent RCTs found very promising results when using probiotics to treat PCOS symptoms, with several studies reporting a reduction in androgen levels as well as improving metabolic markers [23, 24]. A recent metaanalysis of RCTs conducted until 2019 with this topic in mind also found an improvement in metabolic and hormonal markers in women with PCOS across 11 analyzed studies [25], as did another review on the benefits of various nutritional approaches [26].

### Hypothesis and objectives

The working hypothesis of this randomized controlled trial (RCT) is an improvement of PCOS symptoms and androgen levels after six months of probiotic intervention. To that end, the trial is designed to primarily compare the probiotic intervention to a placebo treatment and secondarily to a standard non-hormonal treatment option such as metformin. To our knowledge, this RCT is the first trial to compare the effects of probiotics to placebo and to include metformin as a benchmark treatment arm.

Two other secondary objectives are to determine the prevalence and impact of equol production in women with PCOS compared to previous reports in literature based on the general population [27, 28]. The fourth secondary objective is to obtain biopsy samples from 30 voluntary participants across all three treatment arms from the stomach, the duodenum as well as the sigmoid colon in order to assess potential differences between the luminal and mucosal microbiome composition in the study subjects.

## Methods and analysis

### Study design

This phase IV trial is monocentric, randomized and double-blinded with one additional open-label treatment arm serving as the positive control. Two randomizations are performed. In the first randomization, participants are randomized in a 2:1 ratio to either the double-blind part or open-label metformin part. This open randomization is performed via the web-based randomization service “Randomizer” (Randomizer; Institute for Medical Informatics, Statistics and Documentation, Medical University of Graz, Austria; available at: www.randomizer.at, accessed: September 3, 2021).

The patients who are randomized to the double-blind part are further randomized in a 1:1 ratio to either the probiotic group or the placebo group. The second randomization as well as the allocation concealment is performed by Winclove Probiotics B.V, Netherlands. To ensure that the 30 participants undergoing endoscopic procedures are balanced over the three groups, both randomizations are stratified for endoscopy (yes/no). Both randomizations are performed at visit 1.The study takes place at Graz University Hospital, Department of Internal Medicine, Division of Endocrinology and Diabetology, Endocrinology Outpatient Clinic.

The treatment arms are the following:

Probiotic (number n = 60).Probiotic placebo (n = 60).Open-label metformin (500 mg twice daily, n = 60).

The framework of the study is to show that the effects of the probiotic intervention are superior to the placebo arm. The metformin arm serves as a standard benchmark treatment arm and positive control. The study design is outlined in Fig. 1. This study protocol adheres to the SPIRIT recommendations.

**Fig. 1 Fig1:**
[figure not shown]
Study design of the ProPCO-RCT study; First, the participants´ inclusion/exclusion criteria are determined with detailed patient histories, questionnaires and blood analysis at the screening visit. Then, 30 out of the total 180 participants voluntarily submit to an endoscopy in order to obtain gut biopsy samples for detailed microbiome analysis. Next, all participants perform a soy challenge test and a gut permeability test at home and collect stool and urine samples, which they return at visit (1) There they will be randomized into either the open-label metformin arm or the double-blinded probiotic-placebo arms, with the 30 endoscopy participants being allocated equally across the three groups. If they are randomized into the probiotic or placebo groups, they receive a randomized package containing the blinded trial substances. They then take the study medication for 6 months, before repeating both the endoscopies and the tests at home and returning for visit (2) There all assessments from the screening visit are repeated. Participants of the probiotic and placebo arms may prolong their participation by taking the probiotic product in a 6-months follow-up period, before returning for the final follow-up visit, which is identical to the visit 2; w endo: with a scheduled endoscopy visit; wo endo: without a scheduled endoscopy visit;

### Timeline

For this purpose, potential participants have a screening visit, where participants give written informed consent, blood and urine samples are collected and extensive patient history as well as questionnaires on PCOS symptoms, probiotic intake, depression symptoms and diet are collected. A soy challenge test as well as a functional gut permeability test are scheduled at home, requiring the participants to take urine and stool samples. For the soy challenge test, participants consume 2 × 250 ml soy drinks for two consecutive days, followed by urine sample collection at home each morning the day after soy consumption, similar to Setchell et al. [29]. In the morning of the second urine collection day, participants then drink a sucrose-mannitol-lactulose solution followed by 5 h of urine collection to measure gut permeability. Stool samples are collected before and after soy consumption.

At the first visit (taking place four weeks at the latest after the screening visit), participants deliver the collected stool and urine samples and receive a randomized package of intervention product, which they will take for the next six months. The probiotic and placebo arms get 200 sachets each respectively, to be taken once daily. The metformin group receives 400 tablets of 500 mg metformin, to be taken once daily for the first 7 days of intervention before increasing the dosage to twice daily.

Participants are asked to document any significant health changes or dietary intakes as well as the first day of each menstrual cycle. The intervention is scheduled to last 161 to 180 consecutive days, depending on the date of the second visit.

At the end of their intervention, they will repeat the isoflavone challenge and the functional gut permeability tests at home and deliver the respective samples to the outpatient clinic at their second visit (taking place 24–26 weeks after the first visit). There, the blood and urine tests from the screening visit will be repeated.

Participants in the blinded arms of the trial have the option to further take part in a follow-up period of an additional six months, during which they would take the probiotic formula (without placebo), followed by a follow-up visit scheduled one year after trial enrollment.

In addition, two gastro-/sigmoidoscopies each will be performed at the beginning and the end of the intervention period in 30 voluntary participants (10 from each treatment arm planned) in order to obtain biopsy samples from the stomach, duodenum and sigmoid colon. These samples are used for the assessment of the mucosal gut microbiome as opposed to the luminal gut microbiome composition in stool samples. An overview of the timeline and visit schedule is provided in Table 1.

**Table 1 Tab1:** Overview of number of visits and outcome assessments

Visits	Screening visit	Endoscopy 1	Visit 1	Endoscopy 2	Visit 2 End of Intervention	Voluntary follow-up
Weeks +/- 3 or more days	(-4)-(-1) (+/-3 days)	-1 (+/-3 days)	0 (+/-3 days)	24–26 (+/-3 days)	26 (+/-3 days)	52 (+/-3 days)

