**Patient history**						
Extensive patient medical history	x					
Changes in medical history			x		x	x
PCOS history and symptoms	x				x	x
**Randomisation**			x			
**Endoscopic procedure**		x		x		

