**Laboratory**						
Hormone panel	x				x	x
Oral glucose tolerance test	x				x	x
Safety lab (not an endpoint)	x				x	x
Coagulation safety lab	x					
FACS	x				x	x
P800 and PAX gene tube	x				x	x
Inflammation, gut permeability	x				x	x
Urine tests	x				x	x
Pregnancy tests	x				x	x
Biobank samples	x				x	x
**Isoflavone intake test**	Between first and screening visit			Before the second visit		
**Functional gut permeability test**	Between first and screening visit, after isoflavone intake test			Before the second visit, after isoflavone intake test		

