### Eligibility criteria

In order to be eligible for the trial, women should be between 18 and 45 years of age, they should have at least two out of three Rotterdam criteria and they have to sign the informed consent form before starting the trial.

Women can only participate if they do not have: hyperandrogenism of any cause other than PCOS; pregnancy or nursing period; soy or other allergies related to the study procedures; type 1 diabetes; chronic inflammatory bowel disease, history of cancer in the gastrointestinal tract or acute gastrointestinal infection; any malignancies requiring treatment in the 3 years preceding trial participation; any other chronic disease requiring medical check-ups or hospital treatments at least once every three months (exception: type 2 diabetes); major surgery in the gastrointestinal tract (e.g. colectomy, gut segment excision with stoma surgery, Whipple´s surgery; removal of the appendix or the gall bladder is not considered major surgery); chronic therapy with antidiabetic drugs, proton pump inhibitors, systemic intake of steroids or hormonal contraceptives in the six months preceding trial participation; antibiotic treatment within three months prior to trial procedures; alcohol or drug abuse.

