### Adherence to study procedures

Due to stringent exclusion criteria and the long duration of the intervention period, we expect many participants to not be able to fully adhere to study procedures as outlined in the study protocol due to for example requiring antibiotic treatment or an unscheduled pregnancy. The study was planned and submitted prior to the COVID-19 pandemic outbreak, and therefore in many cases appointments and schedules for trial procedures may need to be altered. In such a case, deviations from the study protocol are documented in the CRF and participants may still continue with trial participantion. For the purposes of statistical analysis, all participants will be considered for the intention-to-treat analyses. The same statistical analyses will be applied additionally for the subpopulation that completely adhered to the trial protocol.

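### Pregnancy is an exclusion, but the only pregnancy test marked before randomisation is at screening, up to four weeks before randomisation and dispensing

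*Protocol article*

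**What the plan says.** All references are to the protocol article.

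- **Exclusion.** Eligibility criteria lists "pregnancy or nursing period" among the reasons a woman cannot take part.
- **When eligibility is settled.** The legend of Fig. 1 says that "the participants´ inclusion/exclusion criteria are determined with detailed patient histories, questionnaires and blood analysis at the screening visit".
- **Test schedule.** In the Laboratory block of Table 1, the row "Pregnancy tests" is marked at the screening visit, visit 2 and the voluntary follow-up. Endoscopy 1, visit 1 and Endoscopy 2 are blank.
- **Interval.** Timeline: "At the first visit (taking place four weeks at the latest after the screening visit), participants deliver the collected stool and urine samples". Table 1 puts screening at week -4 to -1 and visit 1 at week 0, each with a tolerance of 3 days. Endoscopy 1 is at week -1.
- **What happens at visit 1.** Study design: "Both randomizations are performed at visit 1". Timeline adds that participants then "receive a randomized package of intervention product, which they will take for the next six months".
- **What is rechecked at visit 1.** Apart from randomisation, Table 1 marks one item there: "Changes in medical history".

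**The concern.** An exclusion protects participants only if it still holds when treatment is assigned. Here it is verified at screening and, as far as the published schedule goes, not verified by test again until visit 2, 24 to 26 weeks after visit 1. A woman who conceives between screening and visit 1 can be randomised, with a one-in-three chance of metformin, and be handed a six-month supply. If she is one of the 30 endoscopy volunteers, she can also undergo the first endoscopy. None of this would breach the schedule.

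The remaining check is a question about changes in history, which depends on the woman knowing. Chronic hormonal contraceptive use in the preceding six months is an exclusion, and oligo-/amenorrhoea is one of the three Rotterdam criteria. For some participants a late period will therefore be a weak signal. If the pregnancy is found later, the section on adherence to study procedures has the deviation documented, lets participants continue and keeps everyone in the intention-to-treat analyses. A test before randomisation would find most such cases while the woman can still be treated as not meeting the criteria.

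**Working it through.** **Step 1: age of the last test at randomisation.** Inputs: Table 1 and Timeline.

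- Nominal gap from screening to visit 1: 1 × 7 = 7 days to 4 × 7 = 28 days. The upper end matches the four-week maximum in Timeline.
- With the 3-day tolerance on screening only: up to 28 + 3 = 31 days.
- With the tolerance on both visits: up to 28 + 3 + 3 = 34 days. Read this way, Table 1 allows more than the text's own maximum.
- Nominal gap from screening to Endoscopy 1 (week -1): 0 to 21 days.

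**Step 2: is the blank cell real?** The same table places the randomisation row and the history-update row correctly under visit 1. The column layout can therefore be trusted, and the blank in the pregnancy-test row is not a reading error. The urine delivered at visit 1 was collected at home for the soy challenge and gut permeability tests; no pregnancy test on it is described.

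**Step 3: expected number.** The documents give no conception rate, so r is an assumption, shown over a range.

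Expected number = 180 × r × (gap in days / 365.25); chance of at least one = 1 − exp(−expected number).

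| Assumed r per woman-year | Gap 28 days: expected | Chance of at least one | Gap 7 days: expected |
|---|---|---|---|
| 1% | 180 × 0.01 × 28/365.25 = 0.14 | 13% | 0.03 |
| 3% | 0.41 | 34% | 0.10 |
| 5% | 0.69 | 50% | 0.17 |
| 10% | 180 × 0.10 × 28/365.25 = 1.38 | 75% | 0.34 |

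The 28-day column is an upper bound for each rate, since it gives all 180 women the maximum nominal gap.

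**Step 4: effect on the analysis.** The plan's own sample size reproduces: a difference of 0.6 pg/ml with SD 1.1 pg/ml, 80% power and two-sided 5% needs 53.7, so 54 per group, and 54/0.90 = 60. Even 1.4 women is 1.4/180 = 0.8% of the trial. Sample size, power and significance level are unchanged whether or not a test is added.

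**The case against.** The strongest reply is that the plan is coherent as it stands. Criteria are determined at screening, pregnancy is tested there, and history is updated at visit 1. The article also condenses a full protocol that is not shown, which may contain a contraception requirement or a further eligibility check. That is fair as to contraception and handling, and nothing here criticises their absence. It does not dispose of the point: the article prints a dedicated row stating when pregnancy tests are done, and that row leaves visit 1 empty.

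Several stronger readings are tempting but are not supported.

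- *Pregnancy is tested only at screening.* True only up to randomisation; Table 1 also marks visit 2 and follow-up.
- *A missed period tells these women nothing.* Eligibility needs any two of three Rotterdam criteria, so oligo-/amenorrhoea is not required, and no proportion is given. The signal is weakened, not absent.
- *Such a woman never met the entry criteria.* She met them when assessed and ceased to meet them afterwards.
- *One to four women would be randomised while pregnant.* That needs 0.5% to 2% per four weeks (180 × 0.005 = 0.9; 180 × 0.02 = 3.6). Over 13 such periods this is about 6% to 23% a year, a high assumption applied at the maximum gap to everyone.
- *The protocol itself expects pregnancies in this gap.* The section on adherence does mention participants "requiring antibiotic treatment or an unscheduled pregnancy", but as a reason for non-adherence over a long intervention period, not between screening and visit 1.
- *The primary comparison is compromised.* A condition present before randomisation is balanced by it in expectation, and the numbers are very small.

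It is also true that a test at visit 1 leaves the following 24 to 26 weeks without a marked test until visit 2. That limits the benefit but does not remove it.

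**Conclusion.** The point holds as a gap between an eligibility rule and the schedule that should enforce it. Before randomisation the exclusion rests on one test, nominally 7 to 28 days old at visit 1, plus a self-reported history update. A woman who has conceived since screening can be randomised and given study product without any departure from the schedule. The expected number is small: about 0.1 to 1.4 of 180 at the full 28-day gap, on an assumed 1% to 10% per woman-year, and fewer at shorter gaps. The reason to act is participant safety and clean eligibility, not validity: the effect on power and on the comparison of probiotic with placebo is negligible. It is worth correcting because the correction is cheap.

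**What to change.** Reconcile the pregnancy exclusion in Eligibility criteria with the Table 1 schedule, so that the exclusion is confirmed at visit 1 before either randomisation. One way is to mark the existing pregnancy-test row at visit 1, using a urine strip at a visit already held. Consider the same for Endoscopy 1. While editing, align the tolerances in Table 1 with the four-week maximum in Timeline, since 31 or 34 days is otherwise possible. If the full protocol already contains a check at visit 1, the change is only to show it in the table.

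The cost is about 180 urine strips, or 180 + 30 = 210 with the endoscopy volunteers, and no extra visit or invasive procedure. The limit is that very recent conceptions would still be missed, so the gap is narrowed rather than closed. How a positive result is handled clinically is for the investigators to decide.

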**Patient history**						
Extensive patient medical history	x					
Changes in medical history			x		x	x
PCOS history and symptoms	x				x	x
**Randomisation**			x			
**Endoscopic procedure**		x		x		
**Examinations**						
Body weight/height	x				x	x
Waist/Hip circumference	x				x	x
Blood pressure, heart rate	x				x	x
Ferriman-Gallwey Score	x				x	x
**Questionnaires**						
Diet (General, vitamin D and calcium)	x				x	x
PCOS	x				x	x
Depression scales	x				x	x
Bristol Stool Scale	x				x	x
**Laboratory**						
Hormone panel	x				x	x
Oral glucose tolerance test	x				x	x
Safety lab (not an endpoint)	x				x	x
Coagulation safety lab	x					
FACS	x				x	x
P800 and PAX gene tube	x				x	x
Inflammation, gut permeability	x				x	x
Urine tests	x				x	x
Pregnancy tests	x				x	x
Biobank samples	x				x	x
**Isoflavone intake test**	Between first and screening visit			Before the second visit		
**Functional gut permeability test**	Between first and screening visit, after isoflavone intake test			Before the second visit, after isoflavone intake test		

### Eligibility criteria

In order to be eligible for the trial, women should be between 18 and 45 years of age, they should have at least two out of three Rotterdam criteria and they have to sign the informed consent form before starting the trial.

Women can only participate if they do not have: hyperandrogenism of any cause other than PCOS; pregnancy or nursing period; soy or other allergies related to the study procedures; type 1 diabetes; chronic inflammatory bowel disease, history of cancer in the gastrointestinal tract or acute gastrointestinal infection; any malignancies requiring treatment in the 3 years preceding trial participation; any other chronic disease requiring medical check-ups or hospital treatments at least once every three months (exception: type 2 diabetes); major surgery in the gastrointestinal tract (e.g. colectomy, gut segment excision with stoma surgery, Whipple´s surgery; removal of the appendix or the gall bladder is not considered major surgery); chronic therapy with antidiabetic drugs, proton pump inhibitors, systemic intake of steroids or hormonal contraceptives in the six months preceding trial participation; antibiotic treatment within three months prior to trial procedures; alcohol or drug abuse.

